Acceptability, feasibility and appropriateness will be evaluated using qualitative data from staff and patients. Staff perspectives will be sought during the pre-implementation and implementation periods (perceptions of current state, views about the intervention and challenges/enablers for implementation) as well as 6 months after the commencement of the post-implementation period (perceived success or failure of the intervention, impact on patient care, staff workloads and job satisfaction and reflections on feasibility and appropriateness of the STAT model for specialist clinics). Patient perspectives of the clinic service will be sought from samples of patients who attend during the pre- and post-implementation periods.

The total cost of implementation will be considered in two parts: (i) Cost of initial backlog reduction (auditing and short-term additional supply) per patient removed from the waiting list and (ii) total cost of clinic operations during the pre- and post-implementation periods. The cost-effectiveness of the STAT programme will determine the incremental cost per percentage of urgent referrals seen within 30 days and routine referrals seen within 90 days, comparing usual care conditions to intervention conditions. Individual patient health service utilisation cost (outpatient services, emergency presentations and health service admissions) will be collected for the 6 months prior to their first clinic appointment and the first 6 months following this appointment, for patients under usual care conditions and for patients under intervention conditions (estimated n=800).

Outcome measures across all aspects of the trial are summarised in table 3.

**Table 3 T3:** Summary of outcome measures and data sources

	Routinely collected data	Consumer interviews	Staff focus groups	Prospective audits

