#### Effectiveness

Linear mixed effects models will be used to analyse data related to the primary outcome with time-point (time since trial start) and time since intervention as factor variables. This allows for the expected nonlinear change over time, as well as an analysis of persistence of intervention and time-averaged intervention effects following the service redesign, consistent with recommendations.^40^ Generalised linear mixed effects models will be used to analyse the secondary outcomes (binomial for proportions and negative binomial for counts to allow for over-dispersion). A random effect for the clinic will be used for all models to account for clustering. Visual diagnostics will be used to assess model assumption validity, and transformations of outcomes or robust estimators will be used as needed. Adjusting for and analysing the association between covariates (eg, referral source and demographic data, including potential indicators of disadvantage such as need for interpreters) and outcomes will also be completed by including these in the mixed-effects models as predictors. Given the small number of clusters, the Kenward-Roger small-sample correction will be used for the df for inference of the fixed effects.^41^

In the event of any system-wide (eg, pandemic) and within-cluster notable disruptions (eg, staffing issues) that are not adequately captured by the baseline random-effects structure and residual variation, a disruption indicator variable will be used for the disrupted time period. This model of adjustment to disruption can also be included as an indicator within affected clusters only. As an additional sensitivity analysis, within-cluster time-series analyses will be conducted to account for localised temporal disruptions while assessing the persistence of intervention effects. R V.4.4.1 (or a newer version if available) will be used for the analyses.

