A cost of implementation and cost-effectiveness analysis will be completed from a health service perspective. A priori subgroup analysis of clinic patient types (urgent vs routine) will be completed as part of the economic evaluation. The cost of implementation will include two parts: (1) the cost of initial backlog reduction and (2) the cost of clinic operations. The cost of initial backlog reduction will be calculated by dividing the total cost by the incremental difference in the number of patients on the waitlist at the end of the pre-implementation period and the number of patients on the waitlist at 30-day post-implementation. The total cost of clinic operations will be calculated using quarterly audits throughout the trial to record all usual care costs (usual care staffing, capital and overhead costs) as well as any additional investment associated with the intervention, less the income derived from activity-based funding received by each cluster. A unit cost will be calculated by dividing the total cost for each cluster in each 3-month period by the number of new patients who receive a first appointment with a clinic within that cluster during that time. Each of these costs will be reported as a cost per cluster and as mean costs (with SD) across clinics. Costing at the service level will enable comparative efficiency measures such as the ratio of inputs to service output. The cost of implementation analysis will be presented as an overall cluster cost, as well as a cluster cost for the pre-implementation period and as a cluster cost for the post-implementation period.

To establish the incremental cost-effectiveness ratio (ICER), pre-implementation to post-implementation, cost differences will be divided by the percentage difference of urgent and routine referrals seen within 30 and 90 days, respectively, to determine the cost per 1% increase in the proportion of patients seen within these thresholds. ICERs will be determined by bootstrapping individual cost and effect data 5000 times, and this will be presented as an ICER value with 95% CIs and visually presented on a cost-effectiveness plane.

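### The ICER is an unadjusted before-after contrast with a bootstrap that ignores specialty, and the backlog unit cost is divided by something other than patients removed

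*Protocol article*

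**What the plan says.** All references are to the Protocol article.

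- **ICER contrast** (Analysis, Implementation): "pre-implementation to post-implementation, cost differences will be divided by the percentage difference of urgent and routine referrals seen within 30 and 90 days", respectively. No period term or concurrent comparison is mentioned.
- **ICER interval** (same section): "ICERs will be determined by bootstrapping individual cost and effect data 5000 times". Neither stratification nor resampling by specialty is mentioned.
- **Intended comparison** (Outcome measures, Implementation outcomes): the cost-effectiveness outcome is described as "comparing usual care conditions to intervention conditions".
- **Effectiveness models** (Analysis, Effectiveness): the primary outcome is modelled "with time-point (time since trial start) and time since intervention as factor variables", and "A random effect for the clinic will be used for all models to account for clustering". The ICER is not described as a model, so neither statement reaches it.
- **Backlog cost, definition** (Outcome measures, Implementation outcomes): "Cost of initial backlog reduction (auditing and short-term additional supply) per patient removed from the waiting list".
- **Backlog cost, calculation** (Analysis, Implementation): total cost is divided by the "incremental difference in the number of patients on the waitlist at the end of the pre-implementation period" and the number 30 days post-implementation.

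**The concern.** In a stepped wedge every specialty moves from control to intervention as time passes. A plain pre-to-post difference therefore contains whatever else changed in demand, funding or practice. Inflating costs by the consumer price index corrects prices only. The plan handles calendar time for the primary outcome but not for the ICER, so the cost-effectiveness result would not rest on the randomised comparison. It could also disagree with the modelled effect on the same threshold proportions. Cost-effectiveness is part of a stated trial aim and is meant to guide funding.

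Resampling individuals treats patients from eight specialties as independent, which may misstate the precision.

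The backlog cost has two incompatible denominators. Net list change also reflects referrals joining the list and ordinary appointments taking patients off it, neither of which is backlog activity.

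**Working it through.** **1. Layout, checked against the plan's own total.** Inputs: 6 months of initial control, steps every 3 months, 6 months of implementation per specialty (Design); 27 months in all (Health economics data); 100 referrals per quarter and two specialties per step (Sample size). This gives 9 quarters. With the two implementation quarters left out, pre/post quarters are 2/5, 3/4, 4/3 and 5/2 for pairs 1 to 4. Total: 7 × 100 × 8 = 5600, the plan's minimum sample.

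**2. Calendar gap.** Pair 1 has pre quarters 1–2 (mean 1.5) and post quarters 5–9 (mean 7), a gap of 5.5. The other three pairs also give 5.5. Pooled over all cluster-quarters the means are 2.43 and 7.57, a gap of 5.14. If only the last two pre and first two post quarters are used, the gap is 4.

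Spurious effect = drift per quarter × gap. The drifts are assumptions:

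| Drift (points per quarter) | Gap 4 | Gap 5.14 | Gap 5.5 |
|---|---|---|---|
| 0.5 | 2.0 | 2.6 | 2.75 |
| 1 | 4.0 | 5.1 | 5.5 |
| 2 | 8.0 | 10.3 | 11.0 |

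For scale, Sample size uses a change from 80 to 90% (10 points) in urgent patients seen within 30 days.

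**3. Bootstrap unit.** Let total variance be 1, ρ the ICC and κ the cluster autocorrelation. The plan gives ρ = 0.1 for waiting time only. Using it for cost and threshold outcomes is an assumption, and so is every κ.

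*All 5600 patients pooled.* Individual-bootstrap variance = 2/2800 = 0.000714. Pairs contribute unequal shares to pre and post (pair 1: 2 against 5 quarters per specialty), so specialty effects do not cancel:

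Var = ρκ × 2(3² + 1² + 1² + 3²)/28² + (56/28²) × [ρ(1−κ) + (1−ρ)/100]

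- ρ = 0.01, κ = 1: 0.000510 + 0.000707 = 0.001217; SE ratio √(0.001217/0.000714) = 1.31.
- ρ = 0.1, κ = 1: 0.005102 + 0.000643 = 0.005745; ratio 2.84.
- ρ = 0.1, κ = 0.6: 0.003061 + 0.003500 = 0.006561; ratio 3.03.

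At κ = 1, nominal 95% intervals cover about 87% (ρ = 0.01) or 51% (ρ = 0.1).

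*Balanced subset of 800* (the estimated number with individual utilisation costs; 50 pre and 50 post per specialty assumed). Bootstrap variance = 2/400 = 0.005. Constant specialty effects cancel:

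Var = 2 × [ρ(1−κ)/2 + (1−ρ)/50]/8

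| κ (ρ = 0.1) | Variance | SE ratio |
|---|---|---|
| 1 | 0.0045 | 0.95 |
| 0.96 | 0.0050 | 1.00 |
| 0.8 | 0.0070 | 1.18 |
| 0.6 | 0.0095 | 1.38 |

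If the effect also varies between specialties, with an assumed variance of 0.025, add 0.025/8 = 0.003125. The ratio is then 1.23 at κ = 1 and 1.42 at κ = 0.8.

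**4. What adjustment costs.** Only quarter 5 holds both conditions (pair 1 post, pair 4 pre). Generalised least squares with quarter terms and a random specialty effect, ρ = 0.1:

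- 800 patients, two adjacent blocks each side, 25 per cell: SE 0.26 SD (κ = 1), 0.31 (0.8), 0.34 (0.6), against √0.005 = 0.071 for the individual bootstrap. That is 3.7 to 4.8 times.
- All seven quarters, 100 per cell: SE 0.104 SD (κ = 1) to 0.185 SD (κ = 0.8), against 0.027.

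**5. Backlog denominator.** Taking 30 days post-implementation as 30 days after the 6-month implementation period ends, the window is about 7 months. At the minimum 400 referrals a year that is 400 × 7/12 = 233 referrals, not all of them waitlisted.

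Net fall = removed − (referrals joining the list − patients taken off by ordinary appointments).

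Illustration with assumed figures, 200 removed:

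- excess of 100 joining: net fall 100, unit cost 200/100 = 2.0 times the cost per patient removed;
- surplus of 100 ordinary appointments: net fall 300, 200/300 = 0.67 times;
- excess of 200: net fall zero, unit cost undefined.

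**The case against.** **Narrow intervals are not certain.** A reader might infer that an individual bootstrap must understate uncertainty with eight clusters. The documents do not support that. Joint resampling of cost and effect needs patients with both, and individual utilisation costs are planned for an estimated 800. If pre and post are balanced, specialty effects are stable (κ of 0.96 or more) and the intervention effect is uniform, the bootstrap is about right or slightly wide. This stands. Against it, Table 2 says the intervention is tailored by specialty, so a uniform effect is unlikely, and the article does not say which patients enter the bootstrap.

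**The 5.5-quarter gap may not apply to costs.** The costing spreadsheet covers 6 months each side. If the blocks used adjoin implementation (Figure 1 is not shown), the gap is 12 months, seasonality cancels and only secular trend remains. This stands, and is why the range starts at 4. No drift rate appears in the document.

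**An adjusted threshold effect may be available anyway.** Binomial mixed models with a clinic effect are planned for proportions. That would put a clustered estimate beside the ICER, but the time factors are stated explicitly only for the primary outcome, and the ICER would still use the raw contrast.

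**The backlog distortion is easily overstated.** A reader might put all 233 referrals on the list. Setting says urgent referrals may be booked directly, and under STAT new patients are booked without a waiting list. The size is therefore unknown, but the two denominators still conflict.

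**The article is condensed.** A fuller economic plan may specify clustered resampling. The article nevertheless states the contrast, the resampled unit and the denominator outright.

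**Conclusion.** The point holds in three parts of differing strength.

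- **Contrast: firm.** The ICER as written is a before-after estimate, with 4 to 5.5 quarters of calendar change in both cost and effect. This follows from the layout and needs no assumed ICC. The size of the bias depends on a drift that the document does not give.
- **Intervals: conditional.** They are too narrow if all 5600 patients are pooled (ratio about 1.3 to 3.0 for assumed ICC 0.01 to 0.1). For a balanced 800 at ICC 0.1 they range from about right to about 1.4 times too narrow, depending on assumed autocorrelation and effect heterogeneity.
- **Backlog denominator: firm as a contradiction.** The direction and size of the error cannot be known in advance.

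A reader might also infer that the plan neglects time and clustering throughout. It does not: the primary effectiveness model addresses both, and the gap is confined to the economic analysis.

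**What to change.** 1. Estimate the incremental effect from all patients with routine data, and the incremental cost, in models with quarter and specialty terms. Obtain joint uncertainty from a cluster-aware or parametric bootstrap. Eight specialties are few for plain cluster resampling, which favours the parametric form.
2. If the unadjusted pre-post ICER is also shown, label it as a before-after, non-randomised estimate.
3. State which patients and quarters supply the cost and effect components.
4. Divide audit and extra-supply cost by the audited number removed or scheduled (Table 3, Fidelity), saying which, and report net list change separately.

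Items 1 to 4 need reanalysis of data already planned, not new collection. The price is precision: intervals become much wider, about fourfold for costs if these come only from two adjacent blocks each side, and the cost comparison may then be close to uninformative. Collecting costs in more blocks would ease this but is extra work. Net benefit curves could be added, but that is a preference, since a cost-effectiveness plane is already planned.

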### Sample size

A minimum average of 400 referrals is expected to be received for each included specialty annually (100 per quarter), resulting in at least 700 patients across the pre- and post-implementation periods for each cluster (minimum total sample, n=5600). With four steps and eight clusters (two clusters per step), this stepped wedge design will be well powered to detect even small-to-moderate effect sizes. For a mean difference of 0.25 SD in waiting time and a conservative ICC of 0.1, with at least 60 referrals per cluster per 3-month time period (which is less than the pro-rata expected number annually), this design is powered at approximately 90% to sufficiently detect a difference at a 5% level of significance.^38
39^ Again, under conservative assumptions, power for detecting significant differences for our secondary outcomes (eg, an increase in the proportion of urgent patients seen within 30 days from 80 to 90%) exceeds 90%. Compared with our findings from STAT implementation in community outpatient services,^27^ our power and sample size assumptions are chosen conservatively to more than compensate for additional heterogeneity or other differences in the specialised clinic setting.

The sample size for quantitative implementation outcomes is based on the duration of the intervention and length of the waiting lists of the included services. The sample size for the qualitative analysis is considered feasible and expected to be sufficient to reach information power.

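### A 95% CI on the ICER ratio can be read plainly only when nearly all bootstrap replicates show both a gain and an added cost; the plan needs a summary that also holds in other cases

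*Protocol article*

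**What the plan says.** In the protocol article, the Implementation part of the Analysis section defines the ICER as a ratio: "cost differences will be divided by the percentage difference of urgent and routine referrals seen within 30 and 90 days, respectively". On uncertainty it says "ICERs will be determined by bootstrapping individual cost and effect data 5000 times", and that "this will be presented as an ICER value with 95% CIs and visually presented on a cost-effectiveness plane". The cost of clinic operations in the same section is taken "less the income derived from activity-based funding received by each cluster".

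Two other places bear on precision. Under Implementation outcomes, individual service-use costs are to be collected "for patients under usual care conditions and for patients under intervention conditions (estimated n=800" in total; the split between conditions and between urgent and routine patients is not given. Under Sample size, the planning example for the threshold outcome is "an increase in the proportion of urgent patients seen within 30 days from 80 to 90" per cent.

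The article does not mention net benefit, an acceptability curve, a value per percentage point, or a rule for replicates with zero or negative effect.

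**The concern.** Cost-effectiveness is a named aim of the trial, and the only numerical statement of its uncertainty is an interval on a ratio. That raises two difficulties.

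First, sign. A saving with more patients seen in time and an added cost with fewer seen in time both give a negative ICER. Even among favourable results the ratio misorders: saving 200 with a gain of 5 points gives −40, while the better result of saving 200 with a gain of 10 points gives −20. Negative cost differences are realistic because income is subtracted and emergency and inpatient use is counted.

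Second, the denominator. When replicates of the effect difference cross zero, the ratio jumps between large positive and large negative values, and its percentiles no longer run from favourable to unfavourable.

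If the effect is smaller than planned, or costs fall, the reported interval could be uninterpretable or read in the wrong direction.

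**Working it through.** The article states no ICER, cost SD or threshold value, so there is no figure of its own to reproduce. The check concerns how the stated summary behaves.

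**Inputs from the article.** Urgent patients seen in time 80% to 90%; about 800 patients with individual cost data; resampling of individuals.

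**Assumptions.** Equal split, 400 per condition. Urgent shares of 20%, 30% and 50% of these give 80, 120 and 200 urgent patients per condition. The value 400 covers the case where all are urgent, or where the effect comes from a larger dataset. Cost differences, their SE and the value per point (λ) are illustrative.

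**Step 1: sign.** (cost −200, effect +5 points) gives −200/5 = −40. (cost +200, effect −5 points) gives 200/(−5) = −40. The ratio is the same for opposite conclusions. Net benefit, λ × effect − cost, at λ = 50 gives 250 + 200 = +450 and −250 − 200 = −450.

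**Step 2: behaviour of percentile limits.** 5000 simulated pairs, independent normal, cost +200 (SE 150):

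| Effect (SE), points | Dearer, better | Cheaper, better | Cheaper, worse | Dearer, worse | 2.5th to 97.5th percentile of ratio |
|---|---|---|---|---|---|
| 10 (2.5) | 91% | 9% | 0% | 0% | −10 to 64 |
| 2 (2.8) | 71% | 6% | 2% | 21% | −904 to 1053 |
| 0 (2.8) | 46% | 5% | 5% | 45% | −1274 to 1052 |

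In the first row the interval can be set against any non-negative threshold, although the size of its negative limit carries no meaning. In the other rows it bounds nothing useful. The extreme limits also vary from run to run.

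**Step 3: how often a trial reaches that state.** More than 2.5% of replicates lie at or below zero when the observed effect is less than 1.96 × SE. By normal approximation the probability is Φ(1.96 − d/SE), with SE = 100 × √[(p₀(1−p₀) + p₁(1−p₁))/n].

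| Urgent per condition | SE, 80% to 90% | Share of trials | SE, 80% to 85% | Share of trials |
|---|---|---|---|---|
| 80 | 5.59 | Φ(0.17) = 57% | 6.00 | Φ(1.13) = 87% |
| 120 | 4.56 | Φ(−0.23) = 41% | 4.90 | Φ(0.94) = 83% |
| 200 | 3.54 | Φ(−0.87) = 19% | 3.79 | Φ(0.64) = 74% |
| 400 | 2.50 | Φ(−2.04) = 2% | 2.68 | Φ(0.10) = 54% |

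**Step 4: the alternative in the bad case.** Effect 2 (SE 2.8), cost +200 (SE 150), λ = 100: net benefit = 200 − 200 = 0, SE = √(280² + 150²) ≈ 318, 95% CI about −623 to +623. This is wide, but finite and ordered.

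**The case against.** **The plane is already planned.** A dearer-and-worse cloud cannot be mistaken for a cheaper-and-better one on it. This stands as far as it goes: the direction will be visible. It does not give the share of replicates in each quadrant or any numerical inference.

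**The type of interval is not stated.** The article does not say percentile, and a condensed article may leave that to the full plan. This stands. Fieller or angle-ordered limits lessen the problem, but a Fieller set becomes unbounded when the effect is not clearly different from zero, and a signed ratio still needs its quadrant.

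**The components will be reported in part.** Threshold proportions are analysed in mixed models, pre- and post-implementation costs are reported, and urgent and routine results are already planned separately. This stands, except that no CI for the cost difference is promised.

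**The estimated 800 patients relate to service-use costs.** Waiting-time effects are tracked in more than 5600 patients. If more patients inform the effect, the rates move towards the last row of Step 3. The article does not settle which patients enter the bootstrap, so a range is shown.

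**Cluster variation.** A reader might infer that ignoring clusters makes every rate in Step 3 too low. That does not follow under individual resampling. If the true SE is 1.5 times the bootstrap SE, the argument of Φ is divided by 1.5, so rates move towards 50%. At 80% to 90%, 57% becomes Φ(0.17/1.5) = 55% and 19% becomes Φ(−0.87/1.5) = 28%. At 80% to 85% with 80 per condition, 87% becomes 77%.

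**Conclusion.** The point holds in conditional form. The sign ambiguity is a matter of arithmetic. The breakdown near zero effect depends on the size and precision of the effect: 2% to 57% of trials at the planned 10-point effect and 54% to 87% at half of it, over 80 to 400 urgent patients per condition. These figures rest on the assumed urgent numbers, an equal split, individual resampling and a normal approximation. They concern urgent referrals only, since the article gives no planning proportions for routine ones.

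A reader might infer that the planned interval can never show whether the STAT model is cost-effective. The article does not support that. At 80% to 90% with 400 per condition, a trial observing exactly the planned effect has a chance of about 0.00003 that a replicate falls at or below zero, and the interval is then readable. Nor could any interval settle the question alone, because no value per percentage point is named. How often an interval would be wholly negative cannot be estimated either, because the article gives no cost figures. The point is an inexpensive improvement to a stated method; it does not invalidate the economic evaluation.

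**What to change.** Amend the ICER paragraph in the Implementation part of the Analysis section. From the same 5000 replicates, for urgent and routine referrals, report:

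- the cost difference and the effect difference, each with a 95% CI;
- the share of replicates in each quadrant of the plane;
- incremental net benefit with a 95% CI, or an acceptability curve, over a prespecified range of values per 1 percentage point.

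Give the ICER as a point estimate, with a CI only when essentially all replicates lie where both differences are positive. Otherwise state dominance, or say that the ratio is not interpretable.

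The cost is wording only; no new data or resampling are needed. The one real burden is that a range of values per percentage point must be chosen and justified, because the plan names none. It is best fixed before results are known.
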